## **MATERIALS & METHODS:**

**Trial design {8}:** It will be a parallel group, quadruple blind-randomized controlled pilot trial annexed with a laboratory based study.

**Study settings & duration {9}:** The clinical trial will be carried out at the Aga Khan University Hospital (AKUH), Karachi, Pakistan. The total duration of the study is expected to be 6 months i.e. August 2020-January 2021. The viral PCR tests will be done at main AKUH clinical laboratories whereas the immunological tests (cytokine analysis) will be done at the Juma research laboratory of AKUH. The study protocol is already registered at [www.clinicaltrials.gov](http://www.clinicaltrials.gov) with ID# NCT 04341688.

**Sampling technique & Eligibility criteria {10}:** Non probability, purposive sampling technique will be followed to identify a total of 50 participants for this study. The inclusion criteria are laboratory confirmed COVID-19 positive males or females (in the age range of 18-65 years), with mild to moderate disease, already admitted in the AKUH. Subjects who have more than 7 days of the onset of COVID-19 symptoms, edentulous patients, subjects with low Glasgow coma score, intubated patients, history of radiotherapy or chemotherapy will be excluded. Patients who are being treated with any form of oral or parenteral antiviral therapy will be excluded. Patients with known pre-existing chronic mucosal lesions such as lichen planus will also be excluded. Patients who are allergic to the study drugs (Povidone-Iodine, Hydrogen Peroxide, Neem Extract or Hypertonic Saline) will also be excluded.

**Intervention {11a}:** Group A (n=10) patients on 10 ml gargle and nasal lavage using 0.2% Povidone-Iodine (Betadiene® by Aviro Health Inc./ Pyodine® by Brooks Pharma Inc.) for 20-30 seconds, thrice daily for 6 days. Group B (n=10) patients will be subjected to 10 ml gargle and nasal lavage using 1% Hydrogen peroxide (HP® by Karachi Chemicals Products Inc./ ActiveOxy® by Boumatic Inc.) for 20-30 seconds, thrice daily for 6 days. Group C will comprised of (n=10) subjects on 10ml gargle and nasal lavage using Neem extract solution (*Azardirachta indica*)

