formulated by Karachi University (chemistry department laboratories) for 20-30 seconds, thrice daily for 6 days. Group D (n=10) patients will use 2% hypertonic saline (Plabottle® by Otsuka Inc.) gargle and nasal lavage for a similar time period. Group E (n=10) will serve as positive controls. These will be given simple distilled water gargles and nasal lavage for 20-30 seconds, thrice daily for six days. For nasal lavage, a special douche syringe will be provided to each participant. Its use will be thoroughly explained by the data collection officer. After each use, patient is not supposed to eat, drink or mouth rinse for next 30 minutes.

**Discontinuation of intervention {11b}:** Patients who develop rashes, or any other mucosal reaction in oral mucosa or patients who do not wish to continue with the gargles and nasal lavage will be discontinued in the study.

**Compliance on intervention {11c}:** The data collection officer will monitor the amount of gargling solution consumed on daily basis to record the patient compliance on intervention. And once the study is over, the residual bottle will be collected and sent to the incineration. Similarly, any unused/ partially used study drug bottle will be destroyed via incineration.

**Concomitant care {11d}:** Study participants will continue to get their needed routine inpatient medical/pulmonology care concomitantly as per the individual requirements under the care of the attending physician(s).

**Outcomes {12}:** Primary outcome is the reduction in the intra-oral viral load confirmed with real time PCR. Secondary outcome is the change in inflammatory biomarkers (IL-2, IL-4, IL-6, IL-10, TNF- $\alpha$ , IFN- $\gamma$  and IL-17) profiles in the five study groups.

**Participants' timeline {13}:** The timeline has been added as a flow diagram at the end of the protocol. Please see figure 1 on page no. 15.

**Sample Size {14}:** As there is no prior work on this research question, so no assumptions for the sample size calculation could be made. The present study will serve as a pilot trial. We intend to study 50 patients in five study groups. For details, please refer to figure 1 on page no. 15.

**Recruitment {15}:** Patients who are laboratory confirmed COVID-19 within 7 days of the onset of their symptoms who are already admitted as inpatient at the Aga Khan University Hospital, Karachi, Pakistan will be contacted for a voluntarily participation in the study.

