**Group allocation/ Randomization {16a}:** The assignment to the study group/ allocation will be done using sealed envelope method under the supervision of Clinical Trial Unit (CTU) of Aga Khan University, Karachi, Pakistan. The patients will be randomized to their respective study group immediately after the eligibility assessment and consent administration is done.

**Allocation concealment {16b}:** All the study drugs will be kept in identical dark colored bottles so that the intervention is masked.

**Implementation {16c}:** The Neem extract (*Azadirachta indica*) will be compounded at the Chemistry department, University of Karachi, Pakistan. This will be arranged from there whereas other drugs are stored at AKUH pharmacy/ distribution department. The CTU will ensure that only labels mentioning A, B, C, D or E are pasted on the bottles.

**Blinding/ masking {17a}:** Study will be blinded in quadruple. Patients, intervention provider, outcome assessor and the data collection officer will be blinded. The groups will be labelled as A, B, C, D or E. The codes of the intervention will be kept in lock & key at the CTU and will only be revealed at the end of study or if the study is terminated prematurely.

**Un-blinding {17b}:** Although, un-blinding is not permissible, however, if a participant recognizes the intervention using his/her prior knowledge or experience; they will still be encouraged to continue with the study drug till the end of the study. But if any patients develops a serious reaction to the intervention drug, then un-blinding will be done. The principal investigator will consult CTU and with their permission and taking primary attending physician onboard, un-blinding for the patient in question will be done. This will be documented on the proforma.

**Specimen collection {18a}:** The baseline oral swab will obtained (by a trained data collection officer using the required PPEs) from the posterior pharyngeal wall/ tonsillar area of the study participant on day one before initiating the gargles. Study participants will continue to use the

gargle and nasal lavage for 6 days. The end-point oral-pharyngeal swab will be taken on the day 7. Participants will be provided with a protective hood so that they themselves don't generate aerosols in the immediate vicinity while carrying out the gargling and nasal lavage. For nasal lavage, they will use the special douche syringe as described earlier.

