At recruitment stage, we will use restriction i.e. only those COVID-19 positive subjects will be recruited who have no other major co-morbidities. At intervention assignment, the random group allocation will ensure even distribution of the confounders in the study groups, thus their differential effect on the outcome will be taken care of. At analysis stage, we will employ GEE regression analysis (as described above) to account for biases and confounders and lastly, the subset analysis will stratify the data and nullify the effect of biases.

Interim analysis {20b} is not planned on account of a short duration of the study. Intention to treat analysis (ITT) will be adopted for missing data and protocol violations or deviations by uncompliant patients. {20c}

**Data monitoring {21a}:** It will be done bimonthly at two levels. The data monitoring committee comprising of principal and co-investigators will be responsible for the monitoring the data at the primary level whereas the CTU at the university level will oversee and monitor the overall conduct of the study.

The decision of termination of the study {21b} will be made in consultation with the director CTU and the sponsors/ funding agency. The decision will be made after mutual consensus of the parties.

**Harms/ adverse reaction reporting {22}:** The adverse events will be documented for each patient and will be reported bimonthly to the clinical trial unit (CTU). This will also documented in the final report. Sponsor/ funders will be notified of the adverse event using their case report. Due to topical nature of the intervention, most likely harm would be an allergic reaction to any of the study drugs [Povidone-Iodine, Hydrogen Peroxide or Neem Extract (*Azadirachta indica*)]. In case of any serious harm, the advice of the primary attending physician will take precedence over others. However, such patient will be discontinued in the trial, CTU and sponsors informed and un-blinding will be followed as prescribed in section 17b. The role of patient's medical insurance will be decided on individual basis

**Study Audit {23}:** CTU reserves the right of carrying out study audit by internal or external auditors anytime.

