**Informed consent {32}:** Informed consent will be obtained in Urdu (or in English for those who are well versed with the latter) language where the harms and benefits of the gargles and nasal lavage will be explained along with the method of their use in a simple language. The details are stated in the Urdu and English consent forms. The signed consent forms will be retained for the record purpose.

**Laboratory phase for Biological specimen {33}:** Swabs taken from the posterior pharyngeal wall and tonsillar area will be delivered to the laboratory in the transport medium within 4 hours of the specimen collection. The RNA will be extracted in the biosafety cabinet in the BSL-3 laboratory using QIAamp Viral RNA Mini Kit (Qiagen Inc.). Viral RNA will be used as a template in PCR containing following two sets of CDC approved primers and probes targeting COVID-19 virus and Fast Virus 1-Step Master Mix (Thermofisher Inc.). 2019-nCoV\_NI-F (GACCCCAAAATCAGCGAAAT), 2019-nCoV\_NI-R (TCTGGTTACTGCCAGTTGA ATCTG), 2019-nCoV\_NI-P (FAM-ACCCCGCATTACGTTTGGTGGACC-BHQ1) 2019-nCoV\_N2-F (TTACAAACATTGGCCGCAAA) 2019-nCoV\_N2-R (GCGCGACATTCCGAAGAA), 2019-nCoV\_N2-P FAM-(ACAATTTGCCCCCAGCGCTTCAG-BHQ1). To generate standard curve, we will design a synthetic oligo which will contain target sites for the aforementioned forward & reverse primers and probes. We will clone this synthetic oilgo in pGEMT vector after amplifying it through PCR; calculate its copy numbers and use its different dilutions to generate the standard-curve in PCR. Sample Ct values below 35 cycles will be considered as positive. The unknown sample's Ct values will be plotted on standard curve to know the copy numbers.

Cytokine analyses from the collected specimen will be carried out using Cytometric Bead Array (BD Biosciences) on FACS Celesta analyzer. Cytokine bead array detects cytokines using fluorescence labelled beads coated with antibodies. Following incubation of samples with cytokines, a fluorescence labelled antibody is used for the signal detection. The Median Fluorescence Intensity (MFI) is proportional to the amount of analyte present in the sample. All

procedure will be carried as per manufacturer's instructions. Unknown concentration of cytokines will be quantified through a known standards curve of cytokines. Flow JO software will be used for the final analyses.

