### Annexure: 1 (Operational Definitions)

1. COVID-19: An RNA based virus, member of coronavirus family responsible for the current pandemic that has affected nearly 3.7 million cases worldwide. The symptoms are similar to the infection of caused by SARS (severe acute respiratory syndrome). We intend to induct PCR confirmed COVID-19 cases which are within 7 days on infection onset.
2. PCR: Polymerase chain reaction. It will be used to amplify genetic material required for testing. Both the baseline and endpoint specimens will be obtained from posterior pharyngeal wall by trained personnel using proper PPE.
3. Cytokine array: A multiplex ELISA method will be used to detect fluorescence antibody against predefined antigen. We will study the following cytokine profile IL-2, IL-4, IL-6, IL-10, TNF- $\alpha$ , IFN- $\gamma$  and IL-17 among COVID-19 patients in the present study.
4. Neem extract: Biological name *Azardirachta indica*. This has a number of active chemicals that have antiviral activity. A solution will be compounded at University Karachi, Chemistry department laboratory to be used as oral rinse and nasal lavage for COVID-19 patients.
5. PPE: This refers to Personal protective equipment including protective clothing, N-95 mask, eye wear and other garments or equipment designed to protect the person or infection.
6. Gargle: Transiently keeping some fluid in the oral cavity/ oro-pharynx followed by spitting off with an objective of physically rinsing off the mucosal membrane. We will use five different solutions as gargles.
7. Nasal lavage: Passing a fluid in the nose following by sneezing like action to mechanically clear the nasal cavity. The gargling solutions will employed in nasal lavage using a special syringe shown below.

[figure not shown]

Figure 2: Syringe to be used for nasal lavage

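### The day-one pharyngeal swab that anchors the primary outcome need not be positive, so participants with little or no measurable virus at baseline can be randomised and dilute the comparison

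*Protocol*

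**What the plan says.** - **Entry.** Sampling technique & Eligibility criteria {10}: "The inclusion criteria are laboratory confirmed COVID-19 positive males or females". The same section excludes "Subjects who have more than 7 days of the onset of COVID-19 symptoms". Recruitment {15} describes the pool as "Patients who are laboratory confirmed COVID-19 within 7 days of the onset of their symptoms who are already admitted as inpatient", and Annexure 1 adds "We intend to induct PCR confirmed COVID-19 cases which are within 7 days on infection onset". None of these fixes the specimen site, the Ct value, or the interval between the confirming test and day one.
- **Randomisation.** Group allocation/ Randomization {16a}: "The patients will be randomized to their respective study group immediately after the eligibility assessment and consent administration is done".
- **Baseline.** Specimen collection {18a} takes the baseline swab from the posterior pharyngeal wall or tonsillar area "of the study participant on day one before initiating the gargles". Its result is not a condition of entry, randomisation or analysis. The endpoint swab follows on day 7.
- **Positivity.** Laboratory phase {33}: "Sample Ct values below 35 cycles will be considered as positive". The section then says that Ct values are read off a standard curve to give copy numbers.
- **Analysis.** Outcomes {12} makes the fall in oral viral load the primary outcome. Data Analysis {20a} compares it by repeated measures ANOVA, and {20c} states "Intention to treat analysis (ITT) will be adopted for missing data and protocol violations", continuing to deviations by non-compliant patients. No rule covers participants who are negative at baseline.

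**The concern.** The test that admits a participant and the test that starts the outcome are different specimens. A patient can meet every entry criterion, be randomised, and then give a day-one pharyngeal swab at Ct 35 or above. Such a participant has little or no measurable virus for any rinse to remove, so the change recorded will sit near zero, or be an increase, in every arm.

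These participants pull each arm's mean fall towards zero and widen the spread within arms. With 10 per arm there is little room for either. The protocol also tests at p<0.05 and runs its zero-inflated negative binomial subset analysis only if a significant reduction is seen, so a diluted result could end the investigation of a rinse that works where there is virus to clear.

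**Working it through.** **The plan's own figure.** Five groups of 10 give 5 × 10 = 50, as stated. Sample Size {14} gives no power, effect size or SD, so there is no power calculation to reproduce. What follows is an illustration.

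**Inputs.** From the protocol: n = 10 per arm, significance level 0.05, positivity at Ct below 35. Assumed: two-sided testing; share f of baseline-negative participants 5% to 30%; SD σ = 1 log10 among baseline-positives; true difference δ = 1.5 log10 between two arms; change recorded as zero for a baseline-negative participant. The last is a simplification, because the protocol assigns no value to such samples.

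**How many.** The expected number among 50 is 50f: 2.5, 5, 10 and 15 at f = 5%, 10%, 20% and 30%. The chance of at least one in a given arm is 1 − (1 − f)^10: 40%, 65%, 89% and 97%.

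**Dilution.** The expected difference is (1 − f)δ. With δ = 1.5 it becomes 1.42, 1.35, 1.20 and 1.05 log10.

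**Spread.** In an arm with mean fall μ among positives, the variance is (1 − f)σ² + f(1 − f)μ². At f = 10%:
- Falls of 2.0 and 3.5 log10: 0.9 + 0.09 × 4 = 1.26 (SD 1.12) and 0.9 + 0.09 × 12.25 = 2.00 (SD 1.42).
- Falls of 0 and 1.5 log10: 0.9 (SD 0.95) and 0.9 + 0.09 × 2.25 = 1.10 (SD 1.05).

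The loss therefore depends strongly on how far the lesser arm falls in any case, which the protocol does not state.

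**Power.** Simulated two-sample t test, 10 per arm, simulation error about 0.01. Power with f = 0 is 0.89.

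| Baseline-negative share | All patients, lesser arm falls 2.0 | All patients, lesser arm falls 1.0 | All patients, lesser arm falls 0 | Baseline-positive only |
|---|---|---|---|---|
| 5% | 0.73 | 0.80 | 0.85 | 0.86 |
| 10% | 0.60 | 0.71 | 0.82 | 0.84 |
| 20% | 0.42 | 0.57 | 0.74 | 0.78 |
| 30% | 0.30 | 0.43 | 0.64 | 0.72 |

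The last column does not depend on the lesser arm's fall, since only the difference matters once the zeros are removed. It already allows for the smaller arms.

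**Cross-check by formula.** Take δ = 1.25 log10, SD 1 and a lesser-arm fall of 1.0. The power formula for two means, using the mixture variance above, gives 80% with no negatives. With 10%, 20% and 30% negative it gives 64%, 51% and 40% for all patients, against 76%, 71% and 65% in baseline-positives. The pattern is the same.

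**The case against.** Several points on the other side stand.

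- **Age of the confirmation.** A reader might infer that any past positive test admits a patient. The documents do not support that: patients are inpatients with PCR-confirmed disease within 7 days of symptom onset. This should keep the baseline-negative share down, though it does not make it zero.
- **No possible reduction.** A reader might infer that a baseline-negative participant cannot show any fall at all. This is also too strong. Ct 35 is a positivity label, and no rule sets samples at or above it to zero. A sample just past the limit could be given a copy number that falls by day 7. What holds is that little measurable load is left to lose.
- **Bias.** A reader might infer that the comparison is biased towards some arm. It is not: baseline-negatives are balanced across arms in expectation. The harm is dilution, lost precision and chance imbalance.
- **The ITT sentence** is framed around missing data and non-compliance and does not mention baseline-negatives. Still, it is the only analysis principle given, and its ordinary meaning keeps every randomised participant.
- **Other routes.** The planned GEE could adjust for baseline-negative status. With falls of 2.0 and 3.5 log10 this recovers power of about 0.84, 0.79 and 0.71 at 10%, 20% and 30%, practically the same as exclusion. Its covariates are not specified. A SAP, not shown, might define a baseline-positive set, but it would have to be squared with the protocol's ITT statement.
- **Pilot status.** There is no power target to miss. The trial nevertheless tests efficacy hypotheses at p<0.05.
- **Figure 1** is not shown and could contain a screening step; the text on randomisation and specimen collection does not suggest one.

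**Conclusion.** The point holds as a design weakness that is cheap to remove. Neither entry nor the stated analysis requires a positive day-one swab, so participants at or near the detection floor can enter the primary comparison. The estimated difference is diluted by about the share of such participants. Under the assumptions above, at a 10% share, all-patient power is between 0.60 and 0.82 according to the lesser arm's fall, against 0.84 in baseline-positives. The baseline-positive set does at least as well in every scenario examined.

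The size is uncertain. The documents give no baseline-negative share, effect size, SD or expected fall in any arm, and the calculation records zero change for negatives. If the share is very small, or the lesser arm barely falls, the loss is modest.

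**What to change.** 1. In Specimen collection {18a}, take the day-one swab before the randomisation envelope is opened, with the result read later by the blinded laboratory. The reordering removes no one by itself; it makes baseline status a pre-randomisation measurement that cannot depend on the arm.
2. In Data Analysis {20}, define the primary viral-load set as all randomised participants with baseline Ct below 35 on that swab, analysed as randomised regardless of compliance. Keep all randomised participants for a sensitivity analysis and for safety; the sensitivity analysis also preserves any conversion to positive by day 7.

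The cost is a change of order on day one and a short addition to the analysis section. Treatment need not wait for the PCR result. The primary set will have somewhat fewer than 10 per arm (about 9, 8 or 7 at shares of 10%, 20% or 30%), and the estimate will apply to patients with detectable pharyngeal virus at baseline.

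Requiring a positive swab before randomisation would keep 10 per arm, but means waiting for the result and swabbing more patients: 50/0.9, 50/0.8 and 50/0.7, or about 56, 63 and 72.

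### The mucosal-reaction stopping rule in {11b} names only the mouth, although every arm also puts the solution into the nose and the oropharynx

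*Protocol*

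**What the plan says.** Protocol, Discontinuation of intervention {11b}, gives three triggers. Two are reactions: "Patients who develop rashes, or any other mucosal reaction in oral mucosa". The third is the patient's wish: "patients who do not wish to continue with the gargles and nasal lavage will be discontinued in the study".

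Protocol, Intervention {11a}, gives nasal lavage with the gargle in every group. Group A, for example, receives "10 ml gargle and nasal lavage using 0.2% Povidone-Iodine", and the controls in Group E receive "simple distilled water gargles and nasal lavage for 20-30 seconds, thrice daily for six days". Specimen collection {18a} confirms the course, "gargle and nasal lavage for 6 days". Annexure 1, item 7, defines lavage as passing fluid into the nose, and item 6 defines gargling as holding fluid in the mouth or oropharynx.

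Two other sections deal with reactions during treatment. Un-blinding {17b} says that "if any patients develops a serious reaction to the intervention drug, then un-blinding will be done". Harms {22} discontinues a patient after serious harm at any site; other adverse events are documented and reported bimonthly.

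**The concern.** A stated safety rule has a narrower scope than the exposure it is meant to guard. {11b} treats any mucosal reaction in the mouth, however mild, as a reason to stop. The same solution reaches the nasal mucosa and the oropharynx, and the protocol gives no reason for a different threshold there. The withdrawal clause of the same sentence mentions nasal lavage, so the nasal route was in view when the rule was written.

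What is at stake is patient safety. A willing participant could go on applying a blinded agent to nasal mucosa that is known to be reacting, without any protocol rule having been broken. {22} itself expects allergic reaction to be the likeliest harm because the agents are applied topically, so local reactions are foreseen. For Neem, the clinical trials cited in section {34} are of mouthwashes; that section cites no trial of nasal use.

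**Working it through.** The plan has no figure to reproduce. The check sets each possible stopping route against one case: a non-serious mucosal reaction that is known to staff, in the nose or pharynx, in a patient who wants to continue.

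**Exposure, from {11a} and Annexure 1**
- Nasal lavage: Groups A, B, C, D and E, so 5 of 5 arms.
- Oropharynx: reached by gargling under Annexure 1, item 6, again in all arms.
- Participants exposed: 5 arms × 10 = 50.

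**Routes to a stop**

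| Route | Section | Covers the case? |
|---|---|---|
| Rash | {11b} | Only if the reaction is a rash; no site is stated |
| Other mucosal reaction | {11b} | No, limited to the mouth |
| Patient's wish | {11b} | No, the patient wants to continue |
| Serious harm | {22} | No, the reaction is non-serious |
| Un-blinding | {17b} | No, serious reactions only, and it governs the code rather than treatment |
| Adverse-event documentation | {22} | Recorded, but no stop attached |
| Allergy and mucosal-lesion exclusions | {10} | No, these act at entry |
| Routine medical care | {11d} | Possible by clinical judgement, but not a trial criterion |

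No listed trigger covers the case. Two features limit the indirect routes. Bimonthly reporting cannot be relied on to protect a patient whose course lasts 6 days. {11d} concerns inpatient care, while {18b} has discharged patients encouraged to carry on with the study procedures.

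**How a reaction becomes known.** {11c} provides a daily contact on consumption: "The data collection officer will monitor the amount of gargling solution consumed on daily basis". A patient could report a nasal reaction then. A wider stopping rule works only on reactions that someone has reported or seen.

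**Size.** The documents give no rate. Let p be the assumed proportion with a known, non-serious nasal or pharyngeal reaction who wish to continue; the number concerned is 50 × p.
- p = 0%: 50 × 0 = 0.
- p = 2%: 50 × 0.02 = 1, or 0.2 per arm of 10.
- p = 10%: 50 × 0.10 = 5, or 1 per arm of 10.

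These values of p illustrate scale only and have no basis in the documents.

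**The case against.** The strongest reply is that very little is left uncovered. The case must be non-serious, outside the mouth, not a rash, already known, and in a patient who wants to go on. {11b} does not say that its triggers are the only ones, so an investigator or attending physician may still stop the solution. A reader might infer that the protocol obliges patients with nasal reactions to continue, or leaves them unprotected. The text does not support that: what is missing is a mandatory trigger, and nothing forbids a stop.

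A reader might also infer that nobody looks at the nose during treatment. The text shown schedules no nasal inspection, but the timeline figure and the consent forms, which carry details on harms and method of use, are not available here. That inference should not be drawn.

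The pharyngeal part is softer than the nasal part. {18a} calls its baseline specimen an oral swab although it comes from the posterior pharyngeal wall or tonsillar area, so a loose reading of the rule might already include the pharynx. No such reading reaches the nose.

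Finally, {11b} is ungraded. Extending it would stop both gargle and lavage for a trivial nasal reaction, although the primary outcome is intra-oral viral load. Whether a mild nasal reaction should always end treatment is partly a clinical judgement. That objection stands as a cost of the change. It does not explain why the mouth is held to a stricter rule than the nose.

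**Conclusion.** The point holds as a narrow gap in the wording of a safety rule. A known, non-serious mucosal reaction is a mandatory stop in the mouth and not in the nose, nor clearly in the pharynx, for a patient willing to continue. It applies to all 50 planned participants in principle. The number affected in practice is unknown and could be zero.

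The wording is certain; the practical consequence is not. The conclusion assumes that {11b} is applied literally and that no instruction in the unseen consent material fills the gap. A reader might go further and infer bias, lost power or a threat to the primary comparison; nothing in the protocol supports that, and no such effect is claimed. This is a cheap, optional improvement in patient safety. It is a matter for the protocol rather than the SAP, because {11b} itself fixes the rule.

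**What to change.** In {11b}, extend the site so that the trigger is any other mucosal reaction in oral, pharyngeal or nasal mucosa. The site scope of {22} needs no change, since serious harm is already covered wherever it occurs. The edit needs no extra staff, visits or tests. Its downside is possibly a few more treatment stops, each 1 of 10 (10%) of its arm, and possibly uneven between arms if the agents differ in tolerability.

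A separate, secondary clarification: {11b} speaks of discontinuing patients in the study, which leaves open whether follow-up also ends. State that a reaction stops the study solution, and that the endpoint specimen is still collected if the patient agrees. {18a} already fixes its timing: "The end-point oral-pharyngeal swab will be taken on the day 7". This accords with the intention-to-treat analysis in {20c} and avoids losing an outcome in an arm of 10. If it is adopted, check the similar phrase in {22} so that the two sections agree on what discontinuation means.
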